### Outcomes {12}

The primary outcome is a change from baseline of moderate and vigorous physical activity in minutes or steps per week. Therefore, moderate and vigorous physical activity levels are aggregated and measured by one continuous variable. Physical activity is measured continuously with the tracker-based device, and algorithms are implemented to calculate amounts of different intensities [41]. Intensity levels are defined in accordance to intensity classification of Freedson et al. [48].

In addition, physical activity is assessed with questionnaires at four time points (*t*_0_, *t*_1_, *t*_2_, and *t*_3_).

As the analysis of the patient-relevant outcomes morbidity, mortality, and comorbidity of diabetes patients requires long-term studies, which are not feasible in this study due to limited project resources, the clinical outcomes HbA_1c_, body weight, and blood pressure are used as relevant surrogate parameters for these outcomes [13]. Therefore, secondary endpoints are medical parameters (HbA_1c_, TIR (time in range), BMI, and blood pressure). As covariates, psychosocial parameters (generic or diabetes-specific: health-related life satisfaction, self-efficacy, motives, volition, stages of behavioral change, personality, intention, and self-concordance), socio-demographic variables (age, gender, family background, family status, and socio-economic status), physical and mental health, comorbidities, alcohol as well as tobacco consumption, nutritional awareness, usage behavior and user satisfaction (with regard to the activity tracker and smartphone app), diabetes disease and treatment (e.g., medication), participation in external interventions, and severity of the disease are considered. The medical parameters of the healthy individuals are measured at four time points and those of the diabetes patients are collected via routine visits at the cooperating diabetes center. The data about covariates are captured with questionnaires at the same four time points. The items of the questionnaires originate from validated instruments.

In general, changes in the arithmetic means and variances of these mentioned outcomes from baseline are analyzed and compared between the intervention and control groups as well as between the four time points.

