### Sample size {14}

The sample size was calculated according to the primary hypothesis. The correlation between the results of the different measurement times is estimated to be 0.33 based on similar studies [66]. Regarding the effect size, the results of similar studies show that a medium effect can be assumed, which is why the effect size is estimated at *d*=0.5 and *f*^2^=0.15 [27, 28, 33, 66]. A dropout rate of 15% is derived from one of these studies [66]. For a power (1-β) of 0.8 with a significance level of *α*=0.05, assuming an effect size of *f*^2^=0.15, an adjustment with design effect, and a drop-out rate of 15%, a sample size of at least 1642 participants is necessary. With the help of the results of the pre-studies, a more precise calculation of the sample size is possible and the sample size can be adjusted if necessary.

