Since comparisons between participants in the intervention and control groups as well as comparisons of participants at different time points take place, a linear mixed model with two levels will be calculated to test the primary hypotheses [78]. The dependent variable is moderate and vigorous physical activity per week measured with a questionnaire. In the linear mixed model, time (*t*_0_ to *t*_3_) is the intra-class factor, and grouping (intervention group with tracker-based device, intervention group with tracker-based device and digital behavior intervention, and control group) is the inter-class factor [78]. The covariates psychosocial factors, socio-demographic factors, physical and mental health, comorbidities, alcohol and tobacco consumption, nutritional awareness, usage behavior and user satisfaction (with regard to the activity tracker and app), diabetes disease and treatment, participation in external interventions, and severity of the disease are assessed as categorical variables. Random intercepts are assumed while all other effects are regarded as fixed. The null model will be calculated and compared with alternative models regarding its fit via Akaike and Bayesian information criterion [78, 79]. Further, interactions will be considered and will be included in the model if the explanatory power of the model is strengthened. The same analysis will be performed for the assessment of secondary endpoints. Effects of all analyses will be considered significant if *p* < 0.05. All assumptions of the statistical tests will be checked in advance graphically and by appropriate tests. Bonferroni correction will be applied to counteract the problem of multiple testing [80].

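### Multiplicity: Bonferroni is valid, but Holm's step-down tests give the same family-wise error control with equal or greater power, a cheap efficiency gain whose size depends on the family tested

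*Protocol article*

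**What the plan says.** Statistical methods for primary and secondary outcomes {20a} plans a two-level linear mixed model with a three-level group factor (tracker alone, tracker plus digital intervention, control) and four time points. The same analysis is to be repeated for the secondary endpoints. Outcomes {12} lists these: "secondary endpoints are medical parameters (HbA_1c_, TIR (time in range), BMI, and blood pressure". On significance, {20a} says "Effects of all analyses will be considered significant if *p* < 0.05" and then "Bonferroni correction will be applied to counteract the problem of multiple testing". No other multiplicity method is named, and the article gives neither the number of tests nor the set over which the correction runs.

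Sample size {14} works "with a significance level of *α*=0.05" and gives "the effect size is estimated at *d*=0.5 and *f*^2^=0.15". It ends at 1642 participants with 15% dropout.

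**The concern.** With m tests, Bonferroni compares every p-value with 0.05/m. Holm orders the p-values and compares the smallest with 0.05/m, the next with 0.05/(m−1), and so on, stopping at the first failure. No threshold is stricter than Bonferroni's, so no rejection can be lost. The family-wise error stays at or below 5% under any dependence, as with Bonferroni.

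What is at stake is power for the weaker contrasts once a stronger one is clearly positive. The trial asks separate questions about the tracker and about the accompanying digital intervention. Explanation for the choice of comparators {6b} says that the arms were chosen to isolate the effect of the tracker on its own. If the combined arm shows a clear effect, Bonferroni still holds the tracker-alone contrast to the strictest threshold, and Holm does not.

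**Working it through.** **The plan's own figure.** 1642 cannot be rebuilt from {14}, because the value of the design effect is not given. Assuming 1 + 3 × 0.33 = 1.99, d = 0.5 needs 126 before adjustment, and 126 × 1.99 / 0.85 ≈ 295. This does not show 1642 to be wrong, and nothing below depends on how it was reached. I use only 1642 × 0.85 ≈ 1396 evaluable.

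**Inputs**
- Arms: 1:1 allocation with half of the intervention group also receiving the digital intervention (Trial design {8}) gives about 349 / 349 / 698, assuming equal dropout.
- Effects: d = 0.5 from {14}. From Background and rationale {6a}, SMD for moderate to vigorous activity of 0.17 for the wearable alone (reported there as not significant) and 0.28 with a behavioral intervention.
- Assumed: two-sided tests, simple two-mean contrasts, and m = 2 (each intervention arm against control).

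**Step 1. Size of each contrast**
- Standard error in SD units: √(1/349 + 1/698) = 0.0656.
- Expected z: 0.17/0.0656 = 2.59; 0.28/0.0656 = 4.27; 0.5/0.0656 = 7.63.
- Correlation between the two contrasts through the shared control: (1/698)/(1/349 + 1/698) = 1/3.

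**Step 2. Power for tracker alone at SMD 0.17**
- Unadjusted, critical value 1.960: Φ(2.59 − 1.96) ≈ 73.7%.
- Bonferroni, 0.05/2, critical value 2.241: Φ(2.59 − 2.24) ≈ 63.7%.
- Holm: reject if p ≤ 0.025, or if 0.025 < p ≤ 0.05 while the other contrast has p ≤ 0.025. That other contrast (SMD 0.28) passes 0.025 with probability Φ(4.27 − 2.24) ≈ 98%, so nearly all of the 73.7 − 63.7 = 10 points comes back. Simulation with the 1/3 correlation gives 73.4%.

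**Step 3. The planned effect.** At d = 0.5 the expected z of 7.63 is far above 2.24. Power is at least 99.9% even at 0.05/12 for 698 v 698, 349 v 698 and 349 v 349. Holm has nothing to recover.

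**Step 4. How the gain depends on what is true.** Generic case: independent tests, each real effect with 80% power at an unadjusted 0.05.

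| Situation | Power measure | Bonferroni | Holm |
|---|---|---|---|
| m = 3, one real effect | that test | 66.0% | 66.2% |
| m = 6, one real effect | that test | 56.5% | 56.6% |
| m = 2, all real | mean per test | 71.3% | 77.6% |
| m = 3, all real | mean per test | 66.0% | 75.2% |
| m = 3, all real | at least one | 96.1% | 96.1% |

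The last row is equal by construction: the smallest p-value faces 0.05/m under both rules. For the same reason the family-wise error is identical when every null is true (about 4.7% for both with four tests correlated 0.3).

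**The case against.** The strongest reply is that nothing in the plan is wrong. Bonferroni is prespecified, valid and protects under any dependence. That stands, and it limits this point to efficiency.

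A reader might go further and infer that the trial gives away power for nothing. The documents do not support that, for four reasons.
- At the planned d = 0.5 no power is lost. With a single real effect the gain in the cases run is at most 0.3 points, and the chance of at least one rejection never changes.
- The size of the family is unknown. One omnibus group-by-time test would make m = 1, where the two rules coincide. Objectives {7} calls the comparison of the two intervention groups explorative, so it need not sit in a confirmatory family. The set of tests may properly be given in a fuller document that is not shown, and its absence from an article is no fault.
- Bonferroni gives simple simultaneous intervals that agree with its tests. Holm does not, which is a real price. Section {20a} declares effects by p-value and mentions no simultaneous intervals, so the plan as printed does not draw on this advantage.
- The gains in the all-real rows rest on every effect being real at exactly 80% unadjusted power, which is not a figure from this trial.

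What survives is that the dominance is a mathematical fact, and that the effects cited in {6a} for interventions like these are well below 0.5 in places, which is where the choice matters.

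**Conclusion.** The point holds as an inexpensive improvement. Holm is never worse as a test and keeps the same family-wise error. For tracker alone, power rises from about 64% to between 73% and 74%, close to the unadjusted 73.7%. That figure assumes true SMDs of 0.17 and 0.28, 349/349/698 evaluable, two contrasts against control, and two-mean tests standing in for the mixed model. At d = 0.5, or with one real effect, the gain is essentially nil. It would be wrong to conclude that the planned analysis is invalid, that its error rate is inflated, or that a loss of ten points is expected whatever the true effects.

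**What to change.** In {20a}, replace the Bonferroni correction with Holm step-down adjusted p-values at a family-wise level of 5%, applied to the same tests that Bonferroni would have covered, and name those tests. Naming them is necessary because Holm needs a defined set as much as Bonferroni does. Adjusted p-values also fit the existing 0.05 threshold sentence directly.

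The cost is a short change of text, one argument in R, and the published amendment that the protocol's section {25} promises for any change. It should be made before outcome data are analyzed by group. No further participants or data are needed.

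The downside should be stated in the plan. If Bonferroni intervals are reported alongside, a contrast with p between 0.05/m and its Holm threshold can be rejected while its interval includes zero. If intervals that match the tests matter more to the team than the extra power, keeping Bonferroni is defensible, and one sentence giving that reason would be enough.

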### Interim analyses {21b}

Because no potential harm is expected to result from this trial, no interim analyses to terminate the trial are planned.

### Methods for additional analyses (e.g., subgroup analyses) {20b}

Subgroup analyses are planned to be performed by comparing the primary outcomes among healthy individuals, patients with pre-diabetes, and patients with T2DM. Whether the effects of the intervention differ between these subgroups will be tested. Therefore, the health status of the subjects is included as a dummy-variable in the statistical model.

### Methods in analysis to handle protocol non-adherence and any statistical methods to handle missing data {20c}

The collected data will be analyzed in terms of the intention-to-treat (ITT) method, which means that data from all subjects will be assessed because they more realistically reflect the everyday life of the participants [81]. Following the ITT evaluations, the analyses will be carried out again with the per-protocol collective and compared with the results according to ITT using sensitivity analyses [82]. The reasons for withdrawal and drop-out from the trial will be assessed for all groups, and the characteristics of these subjects will be compared between the intervention and control groups. Data will be included in the analyses up to the point of drop-out. The physical activity data measured with activity tracker will be preprocessed using the R package “accelerometry” [83]. Missing and unreliable values will be replaced by the average of neighboring data [83]. For all data, missing values will be quantified and checked if they are not missing at random.

### Plans to give access to the full protocol, participant level-data and statistical code {31c}

At the end of the trial, the aggregated and anonymized data set of the trial will be stored in an appropriate data archive and made available as a scientific use file to other researchers on request to answer similar questions in the field of health research. The data will be available immediately after the end of the study for at least 10 years.

## Oversight and monitoring

### Composition of the coordinating center and trial steering committee {5d}

Not applicable, because no formal committees are needed because of the minimal risks associated with participating in the trial.

### Composition of the data monitoring committee, its role and reporting structure {21a}

No data monitoring committee is needed because of the minimal risks associated with participating in the trial.

### Adverse event reporting and harms {22}

Because of the regular visits to the center in line with routine treatment of the diabetes patients and the regular assessments at four time points for all participants, possible harms associated with the study can be monitored regularly. Furthermore, possible harms and unintended effects of the trial will be reported and assessed by the medical personnel involved in this study. However, the risk of the occurrence of possible harms associated with the trial is regarded as low.

### Frequency and plans for auditing trial conduct {23}

No auditing is planned because the occurrence of possible harms associated with the trial is regarded as low.

### Plans for communicating important protocol amendments to relevant parties (e.g., trial participants, ethical committees) {25}

For any modifications to the protocol that affect the scientific or ethical rigor of the study or the health and safety of the participants, the approval of the Ethics Committee will be obtained before implementation. Furthermore, any changes made to the protocol will be disclosed and published in a formal amendment to the protocol.

### Dissemination plans {31a}

The results of this trial will be made available to interested persons and presented at scientific conferences. All factors that may have influenced the results and their interpretation will be disclosed. All relevant (as well as negative and statistically non-significant) study results will be published in scientific journals and made available to the public on request. The reporting of the results will be based on the CONSORT-EHEALTH (Consolidated Standards of Reporting Trials of Electronic and Mobile EHealth Applications and onLine TeleHealth) guideline for the standardized reporting of the results of trials of internet-based and mobile health interventions [84].

## Discussion

Activity tracker-based consumer electronics are regarded as useful for sustainable improvement of physical activity and for monitoring physical activity in everyday life [20–24, 26, 28]. In addition, with the help of these devices, patients’ adherence to physical activity recommendations can be strengthened [21, 47]. Hence, interventions based on activity trackers have the potential to strengthen physical activity and thus prevent the onset or progression of chronic diseases such as T2DM.

Nevertheless, valid and objectively measured data are needed to understand the complex factors affecting physical activity in daily routine and to increase knowledge about the accuracy as well as reliability of the measurements with these devices [19]. To overcome the limitations of previous studies, such as small sample sizes, short study durations, and lack of analyzing standardized outcomes [20, 26–28, 33–36], the physical activity of 1642 individuals with and without T2DM, half of them wearing the tracker-based device for 6 months, will be assessed and evaluated over 9 months in a randomized, controlled trial. Socio-demographic, socio-economic, physical and mental health-related, and psychological factors that affect physical activity behavior in real-life will be assessed and controlled for in this study. In addition, user behavior related to the tracker and the app and their usability will be studied to evaluate the effects on intervention adherence. Furthermore, the study includes healthy individuals and individuals with pre-diabetes and T2DM to appraise the effects of the intervention against the background of T2DM onset and disease progression. The study uses an interdisciplinary approach, with a team of sports psychologists, sports scientists, health scientists, health care professionals, physicians, and computer scientists, and it involves the processing and analysis of a large amount of data collected with the help of the activity tracker. These factors represent particular strengths as well as challenges in the study.

## Trial status

This is protocol version number 7 14 June 2022. The recruitment is delayed to minimize the risk of a SARS-CoV-2 infection and started in January 2022; the last patient will be enrolled in December 2022. The first results of this study are expected in 2023.

## Data Availability

At the end of the trial, the aggregated and anonymized data set of the trial will be stored in an appropriate data archive and made available as a scientific use file to other researchers on request in order to answer similar questions in the field of health research. The data will be available immediately after the end of the study for at least 10 years.

## Abbreviations

ASKU: Short Scale for Measuring General Self-efficacy Beliefs
BCT: Behavior change techniques
BFI-10: Big Five Inventory
BMZI: Bernese Motive and Goal Inventory
BMI: Body mass index
BSA-F: Movement and Sport Activity Questionnaire
CONSORT: Consolidated Standards of Reporting Trials
CRS: Comfort Rating Scale
FBG: Fasting blood glucose
FFB-mot: Questionnaire for Motor Skills
GEDA: German Health Update
HbA_1c_: Average blood sugar concentrations
ITT: Intention-to-treat
MAUQ: mHealth App Usability Questionnaire
MD: Mean difference
RCT: Randomized controlled trial
(R)CT: Randomized controlled trial or controlled trial
SMD: Standardized mean difference
SOP: Standard operating procedure
TIR: Time in range
VEQ: Volition in Exercise Questionnaire
WHO: World Health Organization
